### Sham ACE group

Patients in the sham ACE group will undergo a similar procedure to the verum ACE group except that nothing will be put into the catgut embedding needles before operation; thus, no catgut will be left under the patients’ acupoint tissue after needle extraction. The prescription of acupuncture will also be the same as that in the verum ACE group.

In the current study, all patients will be treated separately to avoid influencing each other. Both groups will be treated under the same conditions by acupuncturists, who will receive special training before participation in the study. During the entire ACE operation process, the acupuncturists and assistants will not talk about details.

### WL group

The WLC group will not have any intervention. The patients will be asked to receive delayed ACE therapy for free after a waiting period of 20 weeks.

### Magnetic resonance imaging data acquisition

In this study, magnetic resonance imaging (MRI) images of subcutaneous adipose tissue and visceral adipose tissue will be acquired by a MRI scanner (MAGNETOM; Siemens, Munich, Germany) with a matrix body coil of 18 channels at the MRI Center of Shenzhen Traditional Chinese Medicine Hospital. Before scanning, the participants will be trained in deep-breathing exercises. During the scanning process, they will be asked to hold their breath for about 15 s. The sequence parameters are as follows: flip angle, 65°; repetition time (TR)/echo time (TE), 195/3.69 ms; number of excitation (NEX), 1; matrix, 256 × 131; slice thickness, 7 mm; and echo train length, 4. In order to guarantee the passage of the image plane through the center of the vertebral disc between L4 and L5, the MRI data will be acquired from a sagittal scout. Qualitative image analysis will be performed by two independent reviewers as well.

### Outcome measurement

The clinical outcomes will be used to assess patients’ obesity levels and their quality of life. All measurements will be undertaken at baseline (after 8 weeks of treatments, and at 12 weeks of follow-up).

The primary outcome is the change of BMI from baseline. The BMI is calculated as follows: BMI = mass (kg)/(height(m))^2^. According to the BMI-based criteria presented by the WHO and Asia-Pacific classifications in 2000, BMI scores are ranked as “23.0–24.9 (pre-obesity),” “25–29.9 (level I obesity)”, and “more than 30 (level II obesity)”.

The secondary outcomes will include WC, hip circumference (HC), waist:hip ratio (WHR), body fat percentage (BFP), and the WHO Quality of Life (WHOQOL). WC will be measured by a stretch-resistant tape at the midpoint between the top of the iliac crest and the lower margin of the least palpable rib. In addition, HC will be measured around the widest portion of the buttocks using a tape parallel to the floor [23]. BFP will be measured with bioelectrical impedance.

WHOQOL is a widely used questionnaire for measuring physical and mental health status. The WHOQOL scale includes 26 items, involving four domains of patient quality of life: physical, psychological, social, and environmental [24, 25]. The total score ranges from 0 to 100. The lower the score, the poorer the patient’s quality of life.

Other outcome parameters, including basal metabolic rate, blood pressure (BP), heart rate (HR), total cholesterol (TC), triglyceride (TG), and high-density lipoprotein (HDL) levels, will be tested at each time-point.

### Statistical analysis

The statistical analysis will be conducted by independent statisticians who will be blinded to group allocation and intervention methods. Before data analysis, the research group will draw up a statistical plan, including the required data and method of data processing.

Data will be analyzed using SPSS 22.0 software (IBM, Armonk, NY, USA). For MRI data, the images will be analyzed on a workstation (Syngo Multimodality Workplace) for the quantification of VAT and SAT.

Demographic information and levels of measured variables will be analyzed by descriptive statistics. Categorical data are described as percentage (n%) or analyzed using the Chi-square (x^2^) test. Additionally, for continuous variables, if data are normally distributed, one-way analysis of variance (ANOVA) will be used to detect differences among the three groups. Otherwise, the Kruskal–Wallis (K-W) test can be considered. The longitudinal and repeated measured data will be analyzed by the repeated measure analysis.

In this study, SFA is quantified as an area between the outline of the abdominal skin and the outer abdominal muscle, while VFA is defined as the enterocoelia and retroperitoneal region between the inside edge of the abdominal muscles and the spinal front. Detailed methods have been described previously [26–28]. The correlation coefficients between two reviewers who analyzed the same image for SFA and VFA (*n* = 30) were r = 0.99, *P* < 0.001 and r = 0.98, P < 0.001, respectively.

Eventually, the Pearson’s correlation between the changes of SFA and VFA and improvement of clinical variables will be calculated in each group.

For the above-mentioned statistical analyses, a *P* value < 0.05 is considered statistically significant.

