### Sample size

The sample size has been calculated on the basis of results from a previous clinical trial [19]. The primary outcome in the present study is BMI reduction from baseline following 2 months of treatment. According to a previous study [19], in the ACE group, the BMI decreased 1.65 (standard deviation (SD) 1.24); in the sham ACE group, the BMI reduced 0.38 (SD 1.51). Considering a two-sided significance level of 0.05 and power of 0.90, 26 participants in each group are required as calculated by *t* test in G*Power software (version 3, Institute for Experimental Psychology, Heinrich-Heine-University, Germany). A dropout rate of 15% was taken into account so a total of 99 participants will be recruited in this trial (*n* = 33 participants in each group).

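### The BMI analysis names no baseline covariate, lets a normality check pick the test, and does not say which analysis decides the primary result

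*Protocol article*

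**What the plan says.** Two sections of the protocol article define the primary outcome. Outcome measurement says "The primary outcome is the change of BMI from baseline", without a time point. Sample size fixes the time: "The primary outcome in the present study is BMI reduction from baseline following 2 months of treatment".

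The Statistical analysis section gives one rule for all continuous variables: "for continuous variables, if data are normally distributed, one-way analysis of variance (ANOVA) will be used" to compare the three groups. If the data are not normal, Kruskal-Wallis is offered in optional terms. The section then adds: "The longitudinal and repeated measured data will be analyzed by the repeated measure analysis". It names no model, covariate or effect of interest for that analysis, and it ties the analysis to no particular outcome. One significance threshold, P below 0.05, applies throughout. A statistical plan is to be drawn up before data analysis.

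The trial was sized on a difference in mean BMI change between verum and sham: "in the ACE group, the BMI decreased 1.65 (standard deviation (SD) 1.24") against "in the sham ACE group, the BMI reduced 0.38 (SD 1.51"). The section continues "Considering a two-sided significance level of 0.05 and power of 0.90" and concludes that "26 participants in each group are required".

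**The concern.** There are three linked weaknesses.

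1. **Baseline BMI is used only by subtraction.** Change from baseline is usually correlated with baseline itself. An unadjusted comparison of change leaves that part of the variance in the error term. It also lets a chance difference in baseline BMI between arms shift the estimated effect.
2. **A normality check selects the test.** If it leads to Kruskal-Wallis, the result is a comparison of ranks. That gives no difference in BMI units, which is the quantity the trial was sized on, and it takes no covariate.
3. **The deciding analysis is not named.** BMI is measured at baseline, at 8 weeks and at follow-up, so it falls under both the one-way rule and the repeated-measures rule. The three-group test also does not isolate verum versus sham, which is the comparison used for the sample size.

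At stake are a little precision, an interpretable effect estimate, and certainty about which P value is the primary one.

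**Working it through.** **Inputs from the Sample size section.** Mean BMI reductions 1.65 (SD 1.24) and 0.38 (SD 1.51); two-sided alpha 0.05; power 0.90; 26 per group needed; 33 per group recruited, with 15% dropout allowed for.

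**Step 1: reproduce the stated figure.**
- Difference D = 1.65 − 0.38 = 1.27.
- Pooled SD of change = √[(1.24² + 1.51²)/2] = √1.909 = 1.382.
- Standardised difference = 1.27/1.382 = 0.919.
- Two-sample t test (noncentral t): power is 0.890 at 25 per group and 0.901 at 26. The stated 26 reproduces.

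**Step 2: precision left unused.** The documents give neither the between-patient SD of BMI nor its correlation between visits. I assume an SD of 2 to 3.5, equal at baseline and week 8. Then:
- correlation of change with baseline (absolute value): ρ = SD(change) / (2 × SD(BMI));
- share of variance removed by adjustment: ρ²;
- residual SD after adjustment: 1.382 × √(1 − ρ²).

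| Assumed BMI SD | ρ | Variance removed | Residual SD | Power at 26 per arm |
|---|---|---|---|---|
| none (unadjusted) | – | – | 1.382 | 0.901 |
| 2 | 1.382/4 = 0.345 | 11.9% | 1.297 | 0.934 |
| 3 | 1.382/6 = 0.230 | 5.3% | 1.344 | 0.916 |
| 3.5 | 1.382/7 = 0.197 | 3.9% | 1.354 | 0.912 |

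The power figures use the same t-test formula with the residual SD. Spending one degree of freedom on the covariate changes them only in the fourth decimal.

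**Step 3: sensitivity to chance imbalance.** Under the same assumptions the slope of change on baseline is SD(change)² / (2 × SD(BMI)²) in absolute value. After 15% dropout, 33 × 0.85 ≈ 28 per arm remain, so the standard error of the baseline difference is SD(BMI) × √(2/28). A one-standard-error imbalance therefore shifts the verum-sham difference in change by

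1.909 / (2 × SD(BMI)) × √(2/28),

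which is 0.13, 0.09 and 0.07 BMI units for SDs of 2, 3 and 3.5. The planned difference is 1.27.

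**Step 4: several candidate P values.** Data were simulated with no group effect: normal, three arms of 28, three visits, correlation between adjacent visits 0.7 or 0.9, 10,000 runs each.

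| Rule | False-positive rate |
|---|---|
| One-way ANOVA on change | 4.9% to 5.1% |
| ANOVA or Kruskal-Wallis, chosen by a Shapiro-Wilk check | 4.8% to 5.2% |
| Better of ANOVA and the group-by-time test | 8.3% to 8.5% |
| Best of ANOVA, Kruskal-Wallis, group-by-time and overall group effect | 13.8% |

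With normal data the normality check does almost nothing to the error rate. The last two rows apply only if the most favourable result is reported.

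**The case against.** **The outcome already uses baseline.** A reader might infer that the BMI comparison ignores baseline. It does not: both definitions of the primary outcome are changes from baseline, and the sample size uses SDs of change. Under randomisation the unadjusted change score is unbiased. What stands is that no baseline covariate is named.

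**The loss could look much larger than it is.** A reader might take the ANOVA to be run on BMI levels at week 8, where power would be far lower. The text does not support this. The reference to levels of variables belongs to the sentence on descriptive statistics, and an analysis of levels would contradict the stated outcome. Nor is a saving of around 25% plausible here. It needs ρ = 0.5, hence a BMI SD of 1.382/(2 × 0.5) ≈ 1.4, below the whole assumed range.

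**The statistical plan can settle the choice.** The protocol promises one before analysis, and the statisticians are blinded to allocation. Model form is commonly left to that plan. The text can also be read as one-way tests for single time points and repeated measures for data across visits. No passage proposes choosing the best result, so the 8% to 14% rates are a ceiling under misuse and not the plan's error rate. This argument makes the point about several P values secondary. It does not remove it, because the published rules overlap for BMI and the later plan would have to correct them.

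**Conclusion.** The point holds in a limited form. The named analysis is unadjusted, depends on a normality check, and stands beside a repeated-measures analysis with no statement of which one decides the primary BMI result.

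The measurable cost is modest: 4% to 12% of residual variance, or about 0.01 to 0.03 of power at 26 per arm. A one-standard-error imbalance in baseline would shift the estimate by about 0.07 to 0.13 BMI units. These figures rest on an assumed BMI SD of 2 to 3.5, equal at both visits. They would change with the true SD and with the correlation between visits.

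The more practical gain is clarity. There would be one estimate in BMI units for the comparison that was powered, with no doubt about which P value is primary. The stated sample size is not in question here. This is a worthwhile improvement at almost no cost and does not threaten the trial's validity.

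**What to change.** Name one primary analysis, in the statistical plan and in any protocol update:

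- **Outcome:** BMI at week 8, or its change from baseline, with the time point stated the same way in Outcome measurement and Sample size.
- **Model:** ANCOVA, or a mixed model over the two post-baseline visits, with baseline BMI as a covariate.
- **Primary contrast:** verum versus sham at week 8, reported as a difference in BMI units with its confidence interval.
- **Normality check:** drop it as a way of choosing the test. Keep a rank-based analysis as a labelled sensitivity analysis.
- **Other analyses:** label the three-group test and any other repeated-measures analysis as secondary.

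The cost is wording only. Baseline BMI is already collected, and no patients, visits or measurements are added. The change should be dated before any unblinded data are seen.

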## Discussion

It is noteworthy that ACE is extensively applied for weight loss. Although previous studies have shown that ACE might be effective in improving overweight, high-quality trials with rigorous design are still urgently required to assess the effects of ACE on obesity [29]. The results of the present study may contribute to a better understanding of how ACE exerts its potential therapeutic effects on obesity.

Recently, increasing attention has been paid to the visceral fat of obesity, which is related to energy storage, and is considered as an endocrine and paracrine organ, influencing a number of metabolic processes by releasing cytokines and bioactive mediators [30–33]. Body weight can be adjusted by cytokines and mediators. Thus, VFA is a significant indicator for estimating metabolic risk in obese populations [34, 35]. In previous studies, however, the influence of ACE on obesity was mainly assessed by BMI or WC, and a limited number of studies have assessed those influences in relation to VFA. Hence, evaluation in this study is done according to both standard obesity-related indices (BMI, WC, etc.) and VFA in order to clearly illuminate the effects of ACE on obesity.

The purpose of this study is to compare measurement changes after 2 months of treatment with three different intervention methods: verum ACE, sham ACE, and no intervention (WLC group). Several studies [36, 37] have indicated that a sham-controlled design could separate specific and non-specific effects, which may play a pivotal role in evaluating the effectiveness of treatment. Thus, the ACE and sham ACE treatments are both applied to investigate the anti-obesity effects in this study. The sham ACE treatment involves only needle piercing into the acupoints without catgut being fixed; the rest of the procedure is the same as in the ACE group. Thus, it can successfully blind patients and estimators; as a result, it can minimize the placebo effect. In addition, as far as non-specific effects (sham ACE versus no intervention) and bias caused by psychological influences, the third group without any intervention is considered to avoid the placebo effects of group allocation or patients’ beliefs on weight loss. A possible limitation of this trial is that compliance might be difficult for participants due to the long interval from the end of the 2 months of treatment to the follow-up at 3 months. Several actions, such as phone interview, should be taken to improve compliance.

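### The trial is sized on verum versus sham ACE, but the stated three-group test can reach P < 0.05 without any verum–sham difference

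*Protocol article*

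**What the plan says.** Protocol article, Sample size: "The primary outcome in the present study is BMI reduction from baseline following 2 months of treatment". The planning values are a mean reduction of 1.65 (SD 1.24) under ACE and 0.38 (SD 1.51) under sham. The section continues: "Considering a two-sided significance level of 0.05 and power of 0.90, 26 participants in each group are required", calculated by t test. Allowing for dropout, 33 per arm are to be randomised. No waiting-list value enters the calculation.

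Protocol article, Statistical analysis: for normally distributed continuous variables, "one-way analysis of variance (ANOVA) will be used to detect differences among the three groups"; otherwise a Kruskal–Wallis test can be considered. Longitudinal data go to a repeated-measures analysis that is not described further. For all of these a P "value < 0.05 is considered statistically significant". The section also promises a statistical plan before the data are analysed; that plan is not shown.

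Protocol article, Discussion: "The purpose of this study is to compare measurement changes after 2 months of treatment with three different intervention methods". The sham arm is there to separate specific from non-specific effects, and sham versus no intervention is described as addressing the non-specific part.

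**The concern.** The comparison that justifies the sample size does not appear among the stated analyses. A global test of three arms rejects when any arm differs from the others. One arm receives nothing for 20 weeks and cannot be blinded to that. If needling with or without catgut produces the same weight loss through attention, expectation or changed behaviour, both needled arms will differ from the waiting list and the global test will tend to be significant. Read as the trial's efficacy result, that would credit the catgut with an effect that the sham arm was included to rule out.

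The stated power is affected too. The 90% was worked out for a two-group t test, whereas the power of the three-group test depends on the waiting-list mean, for which the protocol gives no value.

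**Working it through.** **Inputs.** From Sample size: means 1.65 and 0.38, SDs 1.24 and 1.51, two-sided alpha 0.05, power 0.90, 26 per group needed and 33 randomised. Assumed, because the protocol gives no figure: a waiting-list mean change of 0 (varied in step 3) and the same SD in all three arms.

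**1. The protocol's own figure.**
- Pooled variance = (1.24² + 1.51²)/2 = (1.5376 + 2.2801)/2 = 1.9089, so SD = 1.38.
- Difference = 1.65 − 0.38 = 1.27; d = 1.27/1.3816 = 0.919.
- Noncentrality at n = 26: 0.919 × √(26/2) = 3.31. The noncentral t distribution gives power 0.901; n = 25 gives 0.890.

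The stated 26 per group is reproduced.

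**2. The three-group test when verum equals sham.** Let both needled arms lose x and the waiting list 0. The grand mean is 2x/3, and the squared deviations of the arm means sum to 2(x/3)² + (2x/3)² = 2x²/3. The noncentrality is λ = n(2x²/3)/1.9089, on 2 and 3n − 3 degrees of freedom. The probability of P < 0.05 from the noncentral F distribution is:

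| x (BMI units) | λ, n = 26 | Probability | λ, n = 33 | Probability |
|---|---|---|---|---|
| 0.38 | 1.31 | 0.16 | 1.66 | 0.19 |
| 1.0 | 9.08 | 0.76 | 11.53 | 0.86 |
| 1.27 | 14.65 | 0.93 | 18.59 | 0.97 |

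Kruskal–Wallis behaves alike: simulated at n = 26 with x = 1.0, it is significant with probability 0.74.

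**3. Power of the three-group test under the planning values.** Verum 1.65, sham 0.38, waiting-list loss w, n = 26, λ = 26 × (sum of squared deviations)/1.9089:

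| w | Sum of squared deviations | λ | Power |
|---|---|---|---|
| 1.0 | 0.807 | 10.99 | 0.84 |
| 0.38 | 1.075 | 14.65 | 0.93 |
| 0 | 1.493 | 20.34 | 0.98 |

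Power therefore lies below or above the stated 0.90 according to an input that the protocol does not set.

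**4. Disagreement between the two tests.** In 20,000 simulated trials with the planning values, w = 0 and n = 26, the three-group test was significant while the verum–sham t test was not in about 8%. So even when the planned effect is real, the two tests are not interchangeable.

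**The case against.** **The article does not call the global test primary, and a statistical plan is to follow.** This is fair. The ANOVA sentence covers continuous variables in general, and the unseen plan may name pairwise contrasts. BMI is also measured repeatedly, so the repeated-measures analysis applies to it; the global test is not the only between-group analysis listed. The Discussion assigns the sham and waiting-list arms roles that imply pairwise reading. A reader might infer that the final analysis will contain no verum–sham comparison; the article does not establish that. What remains is that it states between-group methods that differ from the one used for sizing, and the repeated-measures line names no contrast that would close the gap. A later plan that named verum versus sham would be correcting this text, not filling in a detail.

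**Multiplicity.** A reader might also infer that pairwise tests at 0.05 after the ANOVA would inflate the family-wise error to about 12%, or that a Bonferroni split would cut power from 0.90 to 0.80. Neither follows from the stated methods. The 12% applies to three pairwise tests run without a preceding global test. With exactly three arms, either all are equal, and the global test lets through only 5%, or at most one pair is equal, and one test at 5% is at risk. Simulation of the gated procedure gave 5.0% with all arms equal. With verum equal to sham and both beating the waiting list by 0.38, 1.0 or 1.27, a false verum–sham claim arose in 3.5%, 4.9% or 5.1% of trials (28 per arm). Under the planning values with no waiting-list change, the gated procedure keeps power at 0.90 with 26 per arm. The article mentions no Bonferroni correction, and none is needed.

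**The scenarios are assumed.** This is true, so the range is shown. The high probabilities need a shared non-specific loss well above the 0.38 that the protocol quotes for sham. At 0.38 the figure is 0.16–0.19, which is still more than three times 5%.

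**Conclusion.** The concern holds as a mismatch between the contrast that sizes the trial and the test that is stated. A significant three-group test is not evidence that ACE beats sham. With verum equal to sham, it occurs with a probability from about 0.16 to 0.97 over the cases examined. These figures rest on a common SD of 1.38 and no change on the waiting list, neither of which the protocol states, and on normal data. The logical point needs none of these assumptions.

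A reader might conclude that the trial is too small. It is not: 26 per group gives 0.90 for verum versus sham, and 33 are to be randomised. The defect lies in which comparison the text makes decisive, not in the number of patients.

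**What to change.** In the Statistical analysis section, or in the statistical plan before database lock, state that the primary analysis is the verum-minus-sham difference in mean BMI change from baseline at week 8, with its 95% CI, tested at two-sided 0.05, and estimated from a model that includes all three arms. Make the three-group ANOVA or Kruskal–Wallis test secondary or descriptive. Treat the waiting-list contrasts as secondary as well, for example verum versus waiting list and then sham versus waiting list, each tested only if the test before it is significant. Other orderings that hold the 5% level would also do; what matters is that verum versus sham is named as decisive.

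The cost is one paragraph. No patients, visits or measurements are added, and the primary analysis then matches the comparison behind the stated 90% power.

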**Methods/design:**

A total of 99 eligible patients diagnosed with obesity will be recruited in this study. They will be randomly allocated to either the verum ACE group, sham ACE group, or waiting list (WL) group, with 33 patients in each group. Each patient in the two ACE-based groups will receive eight sessions of treatment, lasting over 8 weeks. The primary outcome is the reduction of body mass index (BMI) after treatment. Secondary outcomes will include waist circumference (WC), hip circumference (HC), waist:hip ratio, body fat percentage, blood lipid level, subcutaneous fat area, visceral fat area, and World Health Organization Quality of Life (WHOQOL). All the outcomes will be evaluated at baseline, at the end of the 8 weeks of treatments, and at 3 months of follow-up. The evaluators and data analyzers will be blinded to group allocation.

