Acupoint catgut embedding (ACE), a complementary and alternative therapy, has been used for several decades to treat a variety of disorders, such as perimenopausal syndrome, chronic urticaria, depressive disorder, refractory insomnia, obesity, sciatica, etc. [17]. ACE involves the weekly infixing of surgical chromic catgut sutures into the subcutaneous tissue of the extremities and abdomen with a specialized needle under aseptic conditions. Owing to the continuous acupoint stimulation by the implanted sutures, ACE was considered to be more effective than ordinary acupuncture or electroacupuncture for patients with obesity [18]. Previous research revealed that the body weight and body mass index (BMI) of obese patients could be remarkably decreased after ACE therapy [19]. Moreover, ACE could adjust the imbalance of obesity-related hormones, e.g., leptin, ghrelin, and adiponectin, to reduce body weight [19, 20]. In addition, visceral fat accumulation is often accompanied by obesity, which has been recently reported to play a vital role in the development of metabolic syndrome, a cluster of diabetes, dyslipidemia, and hypertension [21]. A randomized controlled trial (RCT) conducted by Lei et al. [22] revealed that electroacupuncture treatment could reduce BMI and waist circumference (WC), as well as visceral fat area (VFA). However, whether ACE can improve the VFA of obese patients and what the relationship is between VFA and obesity-related indices are still uncertain. Only a limited number of RCTs have investigated VFA changes with regard to ACE treatment for obesity.

Hence, this study is designed as a RCT to assess the effectiveness and safety of ACE for treatment of obesity.

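### The abstract and the outcome section rank VFA, SFA and lipids differently, and the VFA-to-obesity relationship rests only on small within-arm correlations at P < 0.05

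*Protocol article*

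**What the plan says.** **Outcome ranking.** The abstract's list of secondary outcomes includes "blood lipid level, subcutaneous fat area, visceral fat area, and World Health Organization Quality of Life (WHOQOL"). The Outcome measurement section reads: "The secondary outcomes will include WC, hip circumference (HC), waist:hip ratio (WHR), body fat percentage (BFP), and the WHO Quality of Life (WHOQOL"). It then places total cholesterol, triglyceride and HDL, with basal metabolic rate, blood pressure and heart rate, in a further tier of other parameters. VFA and SFA appear in neither tier.

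**Role of VFA.** The Background gives as the gap to be filled "whether ACE can improve the VFA of obese patients and what the relationship is between VFA and obesity-related indices are still uncertain". The Discussion repeats that the trial assesses VFA alongside the usual indices for this reason, and VFA is one of the article's keywords.

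**Analysis.** For continuous variables the Statistical analysis section plans one-way ANOVA across the three groups (Kruskal–Wallis if not normal), and a repeated measures analysis for longitudinal data. Neither names an outcome. The one analysis that names the fat areas is the last: the Pearson "correlation between the changes of SFA and VFA and improvement of clinical variables will be calculated in each group". A closing sentence applies P < 0.05 to all the analyses listed. No pair is singled out and the correlations are not labelled exploratory.

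**The concern.** There are two separate issues.

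First, two outcome rankings are in print. An article may shorten a full protocol, but here the short abstract contains outcomes that the detailed section leaves out, and lipids hold two different ranks. A later report could cite either list, so VFA or lipids could move up or down once results are known.

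Second, the Background question has two halves: does ACE reduce VFA, and how does VFA relate to obesity indices? For the second half the plan offers only separate correlations in each arm. Each rests on a third of the trial, so moderate associations are easily missed. There are also enough of them, all judged at 0.05, for a few to look significant by chance. A correlation inside one arm says nothing about a treatment effect, and setting one arm's P value beside another's does not test whether the arms differ.

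**Working it through.** **The plan's own figure.** The Sample size section gives: "in the ACE group, the BMI decreased 1.65 (standard deviation (SD) 1.24"); "in the sham ACE group, the BMI reduced 0.38 (SD 1.51"). It then states: "Considering a two-sided significance level of 0.05 and power of 0.90, 26 participants in each group are required".
- Difference 1.65 − 0.38 = 1.27. Pooled SD = √((1.24² + 1.51²)/2) = 1.382. d = 1.27/1.382 = 0.919.
- A two-sided two-sample t test at 0.05 with power 0.90 needs 25.87, so 26 per group. The figure reproduces and is not in question.

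**Evaluable patients.** "A dropout rate of 15% was taken into account so a total of 99 participants will be recruited in this trial", that is 33 per arm. 33 × 0.85 = 28.05, so about 28 per arm and 84 in all. The plan does not print 28; the plausible range is 26 (the stated requirement) to 33 (no dropout).

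**Number of correlations (derived, not printed).** BMI plus WC, HC, WHR, BFP and WHOQOL make 6 variables. 2 fat areas × 6 variables × 3 arms = 36 at one time point.
- Expected false positives if no true correlation exists: 36 × 0.05 = 1.8.
- Chance of at least one, if independent: 1 − 0.95³⁶ = 0.84. In simulation with a correlation of 0.3 to 0.7 among the fat areas and among the clinical variables, it is about 0.82 to 0.59.

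**What one arm can show.** Critical |r| = t/√(n − 2 + t²). At n = 28, t = 2.056 on 26 df, so 2.056/√(26 + 4.225) = 0.374. At n = 26 it is 0.388 and at n = 33 it is 0.344.

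Power by Fisher z = Φ(atanh(r)·√(n − 3) − 1.96). The documents give no r, so these values are assumptions:

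| true r | n = 26 | n = 28 | n = 33 |
|---|---|---|---|
| 0.3 | 0.32 | 0.34 | 0.40 |
| 0.4 | 0.53 | 0.56 | 0.64 |
| 0.5 | 0.75 | 0.78 | 0.85 |

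The 95% interval around an observed r of 0.3 at n = 28 is tanh(0.3095 ± 1.96/5) = −0.08 to 0.61.

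**Pooled, adjusted for arm.** With 84 patients, and two further degrees of freedom deducted for the arm terms, √(84 − 3 − 2) = √79 = 8.89. Power at r = 0.3 is Φ(0.3095 × 8.89 − 1.96) = 0.79, and the interval around 0.3 is 0.09 to 0.49. This assumes a common slope in the three arms.

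**Comparing arms.** If two arms' correlations are compared at 28 each, the standard error on the z scale is √(1/25 + 1/25) = 0.283. The difference detectable with 80% power is (1.96 + 0.84) × 0.283 = 0.79, for instance r = 0 against r = 0.66. The valid comparison is therefore weak, and eyeballing P values is no substitute.

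**The case against.** Several points on the other side stand.

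- A reader might infer that the fat areas are tested only by correlation, with no between-group comparison of VFA. The text does not support this. VFA and SFA are continuous and, according to the abstract, measured at baseline, week 8 and follow-up. The three-group ANOVA or Kruskal–Wallis test and the repeated measures analysis therefore cover them, though not by name.
- A reader might infer that the trial will present a correlation significant under verum but not under sham as a treatment difference. The plan says only that correlations are calculated in each group; it announces no such contrast.
- The count could be pushed to 72 by adding the six other parameters, or doubled by taking both later visits. The plan does not define the clinical variables or name a visit for the correlations, so 36 at one time point is the reading to rely on. The 1.8 also needs every true correlation to be zero, which is unlikely for changes in fat area against changes in BMI or waist.
- Power is respectable if r is 0.5, so the claim that real associations will be missed holds only for moderate ones.
- Working within arms has a sound purpose: it stops differences in arm means from creating an association. A pooled Pearson coefficient without arm in the model would be worse. The arm-adjusted regression keeps this protection.
- A statistical plan is to be drawn up before analysis. Choice of priority pairs and multiplicity control may properly sit there, and their absence here is no fault.
- On the lists, the outcome section omits VFA and SFA but gives them no rival rank. Only lipids carry two ranks. Excluding patients with dyslipidemia does not settle which rank lipids should have.

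What remains is the mismatch between the two lists, and a stated analysis that uses the data less well than it could.

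**Conclusion.** The point holds in a limited form. The two outcome lists disagree and must be reconciled: VFA and SFA are secondary in one and absent from the other, and lipids change rank. This matters because VFA is central to the trial's rationale.

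For the relationship between VFA and obesity indices, the within-arm correlations at P < 0.05 are a poor main analysis. At about 28 per arm, power is 0.34 at r = 0.3, against about 0.79 for an arm-adjusted pooled estimate from the same patients. The figures rest on 15% dropout, six clinical variables at one time point, assumed values of r, and a common slope for the pooled estimate.

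The BMI sample size is unaffected. The documents do not show that the effect of ACE on VFA goes untested, nor that a misleading comparison of arms is intended.

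**What to change.** 1. Before unblinding, make the abstract and the Outcome measurement section agree: list VFA and SFA as secondary in both, and give lipids one rank, which is the sponsor's choice.
2. For the relationship question, make the main estimate a regression of clinical change on fat-area change in all three arms, with arm as covariate. Test differences between arms only through the arm-by-change interaction. Report the within-arm correlations with intervals, labelled descriptive or exploratory, outside the general P < 0.05 rule.
3. Name VFA and SFA in the between-group analysis and adjust that comparison for the baseline value, which is already collected.

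The cost is wording in the protocol and the forthcoming statistical plan; no new data or patients are needed. The downsides are that the pooled estimate assumes a common slope, that the interaction which checks it has little power at this size, and that there will be fewer nominally significant correlations to report.
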